## Abstract

**Background:**

Loss of cognitive function is a significant issue as the world’s population ages. Preserving cognitive function maintains independence in older adults bringing major societal and financial benefits. Lifestyle factors such as diet are modifiable risk factors, which may help preserve cognitive function.

Most nutrition research aimed at preserving cognitive function and metabolic health has focussed on individual nutrients and foods, not allowing for food combinations and interactions. A dietary pattern approach considers the entire diet including its complexity. Previous research investigating dietary patterns and cognitive function has not always considered relevant covariates such as physical activity and the Apolipoprotein E genotype, which are known to have associations with cognitive function.

The aim of the REACH (Researching Eating, Activity and Cognitive Health) study is to investigate associations between dietary patterns, cognitive function and metabolic syndrome, accounting for a range of covariates.

**Methods:**

This cross-sectional study design will recruit older, community-living adults (65–74 years) from Auckland, New Zealand. Dietary data will be collected via a 109-item food frequency questionnaire validated using a 4-day food record. Cognitive function will be assessed using the Montreal Cognitive Assessment (paper based) and the Computerised Mental Performance Assessment System (COMPASS) - a testing suite covering six domains. Additional data will include genetic (Apolipoprotein E ε4) and biochemical markers (fasting glucose, HbA1c, lipids profile), anthropometric measurements (weight, height, waist and hip circumference, body composition using dual X-ray absorptiometry), blood pressure, physical activity (International Physical Activity Questionnaire – short form) and health and demographics (questionnaire).

Dietary patterns will be derived by principal component analysis. Associations between cognitive function and dietary patterns will be examined using multiple regression analysis. Covariates and interaction factors will include age, education, socio-economic status, physical activity, Apolipoprotein E ε4 genotype, family history of dementia or cognitive impairment, and lifestyle factors. Differences between participants with and without metabolic syndrome will also be examined.

**Discussion:**

This study will bring new knowledge regarding associations between dietary patterns and cognitive function and metabolic health in older adults living in New Zealand. This is important for developing nutrition related recommendations to help older adults maintain cognitive function.

## Background

The global population aged over 60 years has doubled in the last 30 years and is expected to double again by 2050 [1]. Independence and quality of life are valued by older adults [2] but these attributes are threatened by poor health in later years [3]. Delaying entry of older adults into aged care residential facilities brings substantial financial benefits to individuals and governments [4]. A key predictor for admission into residential care is impaired cognitive function or dementia [5]. Loss of cognitive function takes away independence, a healthy fulfilling life in final years and can significantly affect family members [6]. Hence, there is a case for preserving cognitive function for as long as possible.

Age-related cognitive decline, mild cognitive impairment and dementia are progressive with limited pharmacological and non-pharmacological treatments available [7]. Without a cure, researchers should strive to discover ways to prevent or slow cognitive decline and the onset of dementia through lifestyle and dietary changes [6].

Age and genetic factors are the most significant risk factors for developing dementia [6]. One specific genetic factor, Apolipoprotein E ε4 (ApoE ε4) not only increases the risk for developing Alzheimer’s Disease [8] and vascular dementia [9] but also puts healthy individuals at risk of a faster cognitive decline as they age [10]. Age and genotype cannot be altered but there are some modifiable risk factors [11] which may slow cognitive decline.

Modifiable risk factors include physical inactivity, smoking, hypertension, obesity, type 2 diabetes mellitus and low educational attainment [11]. Three of these risk factors (hypertension, obesity and diabetes) are components of metabolic syndrome, which further suggests the presence of a “metabolic-cognitive syndrome” via their similar underlying mechanisms through vascular changes [12]. The relevance of lifestyle and diet in cognitive decline and metabolic syndrome is well-recognised [13] and lifestyle and diet is a starting point in the prevention, delay or reduction of the impact of cognitive decline.

Foods and nutrients that may protect against the loss of cognitive function have been identified. These include fruits and vegetables [14–16], fish [15, 16], mono- and poly-unsaturated fats [15, 16] and antioxidants [17, 18]. In contrast, nutrients such as refined carbohydrates and saturated fat may impair cognitive function [15, 19].

Studies of food groups and macro- and micro-nutrients make a valued contribution to nutritional science. However, people consume a diet consisting of many foods, and single nutrient or food group studies may have outcomes confounded by the overall complexity of the diet. The food combinations within a diet can act synergistically, for example altering the bioavailability of nutrients within the body. These changes are not considered in studies of individual food groups or nutrients alone [20]. The study of the combinations and complexities of dietary intake is a more recent development and dietary pattern analysis acknowledges the complexities of food combinations and their associated biochemical interactions as important [21].

Dietary patterns are derived through two processes using dietary data. The first process uses theoretically derived (*a priori*) dietary patterns based on current nutritional knowledge. A dietary index is created, ranking study participants’ adherence to dietary guidelines (e.g. US dietary guidelines) or a dietary pattern (e.g. the Mediterranean diet index) [20]. Several studies show better cognitive function in older adults if their normal dietary intake follow specific features of a diet, for example the Mediterranean diet with its high intake of vegetables, fruits, fish, nuts, cereals and olive oil [16] or the Dietary Approach to Stop Hypertension (DASH) diet, high in vegetables and dairy with a low consumption of saturated fats and sodium [15]. Additionally, the Mediterranean diet, DASH and a Nordic diet, based on Nordic nutrition recommendations, may also have benefits with regards to metabolic syndrome [22].

The second process is an empirically derived (*a posteriori*) dietary pattern. The statistical method of principal component analysis allows measurements on many dietary components to be reduced to measures on a few different dietary patterns [20]. This method enables a better understanding of eating behaviours and a unique view of dietary intake [23] within a population setting. With regards to the older adult, positive associations between empirically derived dietary patterns and cognitive function have been recognised in ‘healthy/prudent’ [24–26] or ‘carotenoid-rich’ [27] dietary patterns in primarily European or North American populations and ‘plant food and fish’ [28], ‘vegetables-fruits’ [29] and ‘snack-drinks-milk products’ [29] dietary patterns in Asian populations. Conversely, negative associations have been noted in cognitive function where a ‘Western’ [25] dietary pattern was consumed. In some instances, no associations were found between cognitive function and ‘traditional’ [26], ‘meat-fish [29], ‘health aware’ [30] or ‘sweet foods’ [30] dietary patterns.

Associations can be attenuated when important covariates are included in the statistical analysis suggesting that the covariate has an effect on the outcome. For example, negative associations between cognitive function and ‘high red meat’ [31], ‘high butter’ [31], ‘processed food’ [32] and ‘traditional’ [30] dietary patterns were weakened when the ApoE ε4 genotype [31], education [32] or childhood IQ [30] were considered in the analysis. Likewise, a positive association was weakened in a ‘whole food’ and ‘Mediterranean style’ dietary pattern with education [32] or childhood IQ [30] as covariates. Consideration of covariates is critical; without it some studies may not be as robust and lead to misinformed conclusions. One of these covariates is the ApoE ε4 genotype. This genotype has been considered in recent research. Analyses show associations are still apparent between dietary patterns and cognitive function when ApoE ε4 is adjusted for [33–35], though in older studies this covariate was disregarded [24–26, 29, 32, 36].

A ‘dietary pattern’ is population specific and dietary patterns have been studied in the New Zealand context [37–42]. However, no studies have investigated dietary patterns exclusively in an older New Zealand population. Therefore, the objectives of the REACH (Researching Eating, Activity and Cognitive Health) study are to investigate associations between dietary patterns and cognitive function in older adults within the New Zealand population. A secondary objective is to investigate associations between dietary patterns and metabolic syndrome.

## Methods

### Study design and participants

The participants in this cross-sectional study will be men and women aged 65–74 years, living independently in Auckland, New Zealand and proficient in English. Participants will be excluded if they are colour blind (due to the computerised cognitive testing requiring colour recognition); have a diagnosis of dementia or any of the following conditions which may impair cognitive function: stroke, traumatic head or brain injury, a neurological or psychiatric condition; or if they are taking medication which may influence their cognitive function. Another exclusion criterion is any event in the last 2 years which had a substantial impact on dietary intake and cognitive function, for example, death or illness of a family member.

A sample size of 350 participants is required to see a medium size effect (Pearson correlation 0.3) with 80% power for the main outcome of a linear association between the cognitive scales and dietary patterns. This sample size is similar to other studies investigating cognitive function and dietary patterns [36]. Data will be collected from 360 participants to allow for missing or incomplete data.

Recruitment and data collection will commence in 2018 and is expected to take 12 months. Participants will be required to attend the Human Nutrition Research Unit, Massey University, Auckland, New Zealand on one occasion. Informed consent forms will be completed at the research facility prior to data collection. The research day involves collecting health and demographic data, blood pressure, anthropometric and physical activity data as per Table 1. A fasted blood sample will be taken prior to a standardised breakfast. Two cognitive assessments will be completed after breakfast. An online food frequency questionnaire (FFQ) and a food diary information video complete the session.

**Table 1 Tab1:** Outcome measures and testing methods for data collection

Variables	Methods
Questionnaires	
Health and demographics	Written questionnaire developed by the researchers – questions regarding: socio-demographic, health, lifestyle and dietary factors.
Physical Activity	International Physical Activity Questionnaire - short form [43]
Anthropometry	
Height, weight, waist and hip circumference	ISAK^b^ anthropometry methods [44] – stadiometer, Tanita Electronic Scales, Lufkin W600 PM flexible steel tape
Muscle mass and fat mass	Dual-emission X-ray absorptiometry, Hologic, Discovery QDR series
Blood Analysis	
Fasting blood glucose	HemoCue Glucose 201RT
HbA1c	Cobas b 101 system [45]
Lipid Profile (total cholesterol, triglycerides, HDL-C, LDL-C^a^)	Cobas b 101 system [45]
Apolipoprotein E ε4	Polymerase chain reaction amplification and direct nucleotide sequence analysis
Clinical	
Blood pressure	Digital Automatic Blood Pressure Monitor, Omron HEM-907
Dietary intake	
Food Frequency Questionnaire	Via Survey Monkey – adapted from Beck et al. [46]
Estimated 4-day food diary	Paper form
Cognitive tests	
Global cognitive function	Montreal Cognitive Assessment (MoCA) [47]
Multiple cognitive domains	Computerised Mental Performance Assessment System (COMPASS-Northumbria University, Newcastle upon Tyne, UK) refer Table 2

^a^calculated

^b^International Society for the Advancement of Kinanthropometry

Funding is provided by the Health Research Council of New Zealand, Grant 17/566. Ethical approval has been granted by Massey University Human Ethics Committee: Southern A, Application 17/69.

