### Statistical analysis

Statistical analysis will be performed using R [58]. Participant data will be described using mean (95% confidence intervals) for normally distributed data, median (25, 75 percentile) for non-normally distributed data, or frequency summary statistics for categorical data. The Shapiro-Wilk test and normality plot will evaluate the normality of distributions.

Dietary patterns will be identified using rotated principal component analysis, a statistical technique to reduce data and produce patterns based on the correlations between food groups [23]. The FFQ food group items will be further collapsed based on other studies investigating dietary patterns [40, 41]. Three separate analyses will be performed: FFQ1 to determine dietary patterns, the 4-day food diary to assess validity of the dietary patterns identified in FFQ1, and FFQ2 vs FFQ1 to assess reproducibility. Orthogonal varimax rotation will be used to facilitate interpretability of components. The number of components retained will be based on the scree plot, eigenvalue (> 1), and interpretability of the dietary pattern. The Kaiser-Meyer-Olkin measure of sampling adequacy and Bartlett’s Test *P* values (to determine the presence of relationships between variables in the factor analysis) will be examined [59]. Labelling of dietary patterns will be based on the interpretation of foods with high factor loadings for each dietary pattern [60].

Multivariate multiple regression analysis [61] will be used to determine the association between dietary patterns and various domains of cognitive function (dependent variable) while considering confounding factors. Possible confounding and interaction factors include: age, gender, ethnicity, education, English as a second language, presence of chronic disease (including metabolic syndrome), socio-economic status, physical activity, body mass index, ApoE ε4 genotype, family history of dementia, smoking, alcohol intake and past dietary intake.

Further analysis will compare dietary patterns of participants with and without metabolic syndrome using multiple logistic regression analysis.

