## Discussion

Age-related cognitive decline is a continuum of natural cognitive changes that may progress into mild cognitive impairment or dementia. Rates of decline differ within a population. Delaying the onset of cognitive decline is the optimal strategy but where there is an earlier on-set the ability to slow the decline is important. Delaying or slowing the decline may be abetted by modifiable lifestyle factors e.g. diet, physical activity. Therefore, an in-depth understanding of the diet (beyond an isolated food and nutrient approach) of older adults is warranted. The REACH study will broaden the current knowledge on dietary patterns and their associations with cognitive function and metabolic health in older adults in a New Zealand context.

Despite the cross-sectional design having limitations e.g. causality cannot be inferred, the study design has several strengths. The study recognises dietary patterns as a measure of the diet and acknowledges the whole diet is greater than the sum of its parts. Extra strengths come from the collection of data on the ApoE ε4 allele, physical activity levels and other known covariates to ensure that any association found is likely to be due to the dietary patterns identified. Additionally, the COMPASS battery of cognitive tests is administered on the computer minimising potential bias associated with administration of these tests by a researcher. The scoring of cognition and the assessment of dietary patterns will be done independently to minimise bias. While there is always bias associated with the type of participant attracted to such studies, the bias will be minimised by using a range of recruiting methods across the wider Auckland region to ensure a range of participant demographics are captured. Furthermore, the size of the study population ensures there is adequate power to detect a meaningful result.

The REACH study is the first to examine dietary pattern associations in older New Zealand adults. This first step paves the way for developing recommendations for New Zealanders to maintain cognitive function, metabolic health and ultimately quality of life as they age. Additionally, it will provide a valuable base for hypothesis generation for future longitudinal studies and / or randomised controlled trials.

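### The sample-size sentence does not fit its own inputs: r = 0.3 with 80% power needs about 85 participants at two-sided 5%, while 350 gives over 99.9% power for r = 0.3

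*Protocol article*

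**What the plan says.** In the Protocol article, Methods, Study design and participants, the sample size is justified in one sentence: "A sample size of 350 participants is required to see a medium size effect (Pearson correlation 0.3) with 80% power". The same sentence ties the power to the main outcome, a linear association between cognitive scales and dietary patterns. It gives no alpha, no sidedness, and no allowance for multiple tests or covariates.

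Two remarks follow. One says the size is similar to that of other studies in the field. The other covers incomplete data separately: "Data will be collected from 360 participants to allow for missing or incomplete data".

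The Statistical analysis section plans the main analysis as follows: "Multivariate multiple regression analysis [61] will be used to determine the association between dietary patterns and various domains of cognitive function". It names 14 possible confounding or interaction factors and does not link that model to the sample size. It plans no multiplicity correction, and it leaves the number of dietary patterns to the scree plot, eigenvalues and interpretability.

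The Discussion later says that "the size of the study population ensures there is adequate power to detect a meaningful result".

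**The concern.** A sample size, an effect size and a power for one correlation are tied together once alpha is chosen. A target of 0.3 at 80% power is usually met with fewer than 100 participants, so 350 stands out as about four times too many for the inputs printed beside it.

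What is at stake is how the study's sensitivity is read. As printed, the sentence tells a reader of a null result that 80% power was available only at a correlation of 0.3. On the usual unadjusted basis, 350 participants give that power at about half of 0.3. No other power calculation in the article would correct the impression.

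**Working it through.** **Inputs from the article (Study design and participants).** r = 0.3, power 80%, n = 350 analysable, 360 enrolled. The allowance from 350 to 360 is 10/360 = 2.8%, so missing data are already dealt with outside the 350.

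**Assumption.** Alpha is not stated. I take two-sided 5% and then vary it.

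**Attempt to reproduce 350.** For one correlation against zero, by Fisher's z:

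n = ((z_alpha + z_power) / atanh(r))² + 3, with atanh(0.3) = 0.3095.

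- Two-sided 5%, 80% power: ((1.960 + 0.842) / 0.3095)² + 3 = 84.9, so **85**.
- One-sided 5%, 80% power: ((1.645 + 0.842) / 0.3095)² + 3 = 67.5, so **68**.
- Two-sided 5%, 90% power: 113. At 95% power: 139.
- Two-sided 1%, 80% power: 125. Two-sided 0.1%: 182.

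The stated figure is not reproduced. 350 / 85 = 4.1.

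**What 350 gives.**

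- Power at r = 0.3: Φ(0.3095 × √347 − 1.960) = Φ(3.81) = 0.9999.
- Detectable r at 80% power: tanh(2.802 / √347) = **0.149**. With all 360 it is tanh(2.802 / √357) = 0.147.
- In reverse, r = 0.15 needs ((2.802) / 0.1511)² + 3 = 346.6, so 347.

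**Could multiplicity explain 350?** The article plans no correction, so these rows are assumptions (Bonferroni, two-sided, 80% power):

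| Assumed number of tests | n for r = 0.3 | Detectable r at n = 350 |
|---|---|---|
| 6 | 130 | 0.185 |
| 21 | 161 | 0.205 |
| 60 | 186 | 0.221 |
| 500 | 237 | 0.249 |

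For 350 to be the 80% power size at r = 0.3, z_alpha would have to be 0.3095 × √347 − 0.842 = 4.92. That is a two-sided alpha of about 8.5 × 10⁻⁷.

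**Could covariates explain it?** For a partial correlation of 0.3 in a regression with 15 to 30 predictors, the noncentral F gives 82 to 83 participants, or 158 at alpha 0.05/21. Covariate degrees of freedom cost almost nothing here.

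**Could a different test explain it?** An overall F test of R² = 0.3² = 0.09 at alpha 5% needs 204 participants with 15 predictors, 229 with 20 and 271 with 30. It reaches 350 only at about 53 predictors.

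**The case against.** The strongest defence is that the article condenses a fuller protocol, so 350 may rest on allowances that were not printed. Such combinations exist. An overall test of R² = 0.09 at alpha 0.05/7 (assuming six domains plus a global score) needs 319 participants with 20 predictors and 374 with 30, which brackets 350. Halving the correlation for dietary measurement error (an assumed factor of 0.5) gives 347; factors from 0.4 to 0.7 give 543 to 176. The article also supports its size by comparison with other studies.

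Part of this stands: the origin of 350 is unknown, and one cannot say which input is at fault. It does not rescue the sentence. The allowances are not stated, an overall test of all predictors is not the linear association that the sentence names, and similarity to other studies does not make 350 the number required for r = 0.3 with 80% power.

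A reader might draw four stronger conclusions, which the article does not support:

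- **That the team meant r = 0.15 and misreported the effect it considers meaningful.** The value 0.15 is solved back from n. The article names 0.3 and calls it medium, and nothing else in it points to a smaller target.
- **That the study is underpowered.** The discrepancy runs the other way.
- **That the Discussion's remark on adequate power is also wrong.** It gives no r, n or power figure, and for r = 0.3 it is true.
- **That a specific adjusted figure, such as 0.205 for 21 tests, describes the planned analysis.** No correction is planned and the number of patterns is not fixed, so any such figure is illustrative.

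**Conclusion.** The point holds as an error in one sentence. At two-sided 5%, the printed inputs give 85 participants, not 350, a ratio of 4.1. The only assumption is alpha, and the conclusion does not depend on it: no single-correlation calculation at a plausible alpha, one- or two-sided, with or without a Bonferroni allowance, comes near 350. With 350, sensitivity at 80% power is about r = 0.15 unadjusted, and about 0.18 to 0.22 if one assumes Bonferroni over 6 to 60 tests.

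The seriousness is moderate. Recruitment, outcomes and analysis are unaffected, and the study exceeds its stated target. It is still worth correcting, because this is the only quantified power claim and it understates what the design can detect.

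**What to change.** Keep enrolment at 360. In Study design and participants, state alpha and sidedness and do one of the following, after the sponsor has checked how 350 was obtained:

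1. Restate the sensitivity, for example: *350 analysable participants give 80% power (two-sided 5%) to detect a correlation of about 0.15, and more than 99% power for a correlation of 0.3.*
2. If 350 includes an allowance for multiplicity, covariates or anything else, state that allowance and show the calculation that yields 350.

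Any multiplicity-adjusted detectable correlation that is added should be labelled as an assumption, with the assumed number of tests. The Discussion can stay as it is. The cost is a sentence or two of wording, with no change to recruitment, data collection or analysis.
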